# Effects of Kami Guibi-tang in patients with mild cognitive impairment: study protocol for a phase III, randomized, double-blind, and placebo-controlled trial

**DOI:** 10.1186/s12906-022-03805-9

**Published:** 2022-12-02

**Keywords:** Mild cognitive impairment (MCI), Amnestic mild cognitive impairment (aMCI), Kami Guibi-tang, Herbal medicine, Herbal formula, Korean medicine, Neuropsychological test, Functional magnetic resonance imaging (fMRI)

## Abstract

**Background:**

Amnestic mild cognitive impairment (aMCI) is often considered a precursor to Alzheimer’s disease (AD) and represents a key therapeutic target for early intervention of AD. However, no treatments have been approved for MCI at present. Our previous pilot study has shown that Kami Guibi-tang (KGT), a traditional herbal prescription widely used in Korean medicine for treating amnesia, might be beneficial for improving general cognitive function of aMCI patients. We will conduct a larger-scale clinical trial to validate the findings of our pilot study and further examine the efficacy and safety of KGT in aMCI.

**Methods:**

This trial is designed as a randomized, double-blind, placebo-controlled clinical trial. A total of 84 aMCI patients will be recruited and randomized into the treatment and control groups. Participants will be administered either KGT or placebo granules for 24 weeks, with a follow-up period of 12 weeks after the last treatment. Primary outcomes will include changes in cognitive performance assessed using a neuropsychological test battery, called the Seoul Neuropsychological Screening Battery, between the baseline, post-intervention visit, and follow-up visit (24th and 36th week, respectively). Secondary outcomes will involve the rate of progression to AD, changes in neuroimaging signals assessed using structural magnetic resonance imaging (MRI), resting-state functional MRI (rs-fMRI), and task-based fMRI, and changes in blood biomarkers measured by the ratio of plasma amyloid-β 42/40 levels (Aβ42/Aβ40) between the baseline and post-intervention visit (24th week). For safety assessments, blood chemistry tests and electrocardiograms (ECG) will also be performed.

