### Outcome

The primary outcome includes changes in cognitive performance after the administration of KGT or placebo granules. SNSB, which is composed of various cognitive tests such as CDR, GDS, and MMSE will be conducted to assess the cognitive function, and changes in SNSB results will be analyzed. The secondary outcomes include the rate of progression to AD at the endpoint, according to NINCDS-ADRDA and CDR-GS score ≥ 1. In addition, we will measure neuroimaging signals and blood-based biomarkers. Structural MRI and functional MRI (fMRI) will be adopted to observe neuroimaging signal changes. The changes in gray matter volume will be measured using structural MRI. Also, Rs-fMRI and task-based fMRI will be performed to compare the changes in functional connectivity among working memory and default mode networks and to measure the changes in brain activation during the face–name association task and one-back working memory task. Levels of plasma Aβ42 and Aβ40 will be measured as blood-based biomarkers. The safety outcomes include electrocardiogram (ECG) and blood chemistry (Na, K, Cl, AST, ALT, BUN, Cr, glucose, LDH, CPK).

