### Assessment

#### K-MMSE and SNSB

K-MMSE will be performed at the screening visit and at 12th week for evaluating the general cognitive status. It is one of the most widely used screening tests to estimate the cognitive functioning [12]. SNSB-II will be conducted at baseline, 24th week, and 36th week, to measure the effect of KGT on cognitive function. Changes in the mean SNSB scores will be analyzed as a primary outcome. SNSB is a neuropsychological test battery most commonly used in South Korea to estimate global cognitive function. The test is composed of various cognitive subtests that assess five domains: memory, attention, language, visuospatial function, and executive function. It also includes other related tests including CDR, K-MMSE, Korean-Instrumental Activities of Daily Living (K-IADL), Barthel-Activities of Daily Living (BADL), and Short-form Geriatric Depression Scale (SGDS) [13]. We will use a modified version of SNSB for dementia (SNSB-D), to obtain a global cognitive function (GCF) score, which is the sum of all the test scores of five domains. The maximum GCF score is 300 points: 150/300 (50%) for memory, 17/300 (6%) for attention, 27/300 (9%) for language, 36/300 (12%) for visuospatial function, and 70/300 (23%) for frontal/executive function [14]. The detailed contents of SNSB-D are presented in Table 3.

**Table 3 Tab3:** Contents of Seoul Neuropsychological Battery for dementia (SNSB-D)

Domains (total score)	Subtests	Maximum points
Attention (17)	Digit span forward	9
	Digit span backward	8
Language & related function (27)	K-BNT	15
	Calculation	12
Visuospatial function (36)	RCFT copy	36
Memory (150)	Orientation	6
	SVLT free/delayed recall	48
	SVLT recognition	12
	RCFT free/delayed recall	72
	RCFT recognition	12
Frontal/Executive function (70)	Motor impersistence	3
	Contrasting program	3
	Go-no-go test	3
	Fist-edge-palm	3
	Luria loop	3
	Categoric word generation	20
	Phonemic word generation	15
	Stroop test-color reading	20
GCF score		300

*K-BNT* Korean short version of the Boston Naming Test, *RCFT* Rey Complex Figure Test, *SVLT* Seoul Verbal Learning Test, *GCF* Global cognitive function

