### Statistics

#### Sample size calculation

The primary outcome of interest in this study is the change in the total SNSB-D score between baseline and post-intervention. The calculation of sample size is based on a superiority test, as the aim of this study is to show that KGT is superior to placebo. Our pilot study of aMCI patients treated with KGT showed that the change in the total SNSB-D score was + 22.47, compared to + 8.36 in the placebo group. The calculated effect size (Cohen’s d) was 0.70. Using G*Power software with a power of 0.80 and a two-sided type I error of 0.05, the calculated total sample size for the current study involves 66 participants, with 33 in each group. The dropout rate was 10% (3 of 33 participants) in the previous study; however, since the current study will take a longer follow-up period, we expect the dropout rate to be 20%. We plan to recruit a total of 84 participants for this RCT (42 participants in each group).

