#### Data analyses

An independent professional statistician, who will also be blinded to the allocation, will perform data analyses using SPSS 20.0 software (IBM, Armonk, NY, USA). Efficacy analyses will be performed using the modified intention-to-treat (mITT) and per-protocol (PP) principles. The mITT population will include participants who have completed at least one examination since the beginning of the intervention. The PP population will include participants who will adhere to the trial protocol and undergo all examinations. Missing data will be adjusted using the last-observation-carried-forward (LOCF) imputation method. A safety test will be performed using the ITT principle. The ITT population will include any participants who will take at least one pack of drugs after randomization. To analyze the efficacy outcome and continuous demographic variables, we will perform the Shapiro-Wilk test to confirm the normality of the data distribution. To analyze the fMRI measures and plasma amyloid beta levels, the paired *t*-test will be used for intra-group comparisons and an independent *t*-test will be used for intergroup comparisons, for normally distributed data. Wilcoxon’s signed rank test will be used for intra-group comparisons and the Mann-Whitney U test for intergroup comparisons of non-normally distributed data. To analyze the scores of the neuropsychological test battery, repeated measures of analysis of variance will be used for parametric data, and the Friedman test for non-parametric data. Categorical demographic variables, conversion to normal cognition or dementia, conversion to positive plasma Aβ42/Aβ40 ratio (< 0.1218), and the incidence of AEs between the groups will be analyzed using the Pearson’s chi-square (χ^2^) test or Fisher’s exact test. Continuous demographic variables will be analyzed using the *t*-test or Wilcoxon signed-rank test. All statistical analyses will be two-tailed, and the significance level will be set at *p* < 0.05.

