## Discussion

This trial was designed based on our previous pilot study. To the best of our knowledge, it is the first confirmatory randomized clinical trial to evaluate the effect of KGT on cognitive function in aMCI patients.

We examined the feasibility of the trial process and the acceptability of KGT treatment in our previous study. Since the results showed a significant improvement in the CDR-SB score in the KGT group, the same neuropsychological test battery, including CDR, was selected as the primary outcome. Moreover, we observed high adherence and drug compliance, with 10% dropout rate. No serious safety concerns were reported.

Several improvements were considered in the planning of the current trial. First, as with most pilot studies, the relatively small sample size limited the statistical power and generalizability. Therefore, we will include a larger sample size in this trial, as calculated based on the results of our pilot trial. Second, there was no follow-up examination of cognitive function after completing the intervention in our previous trial, so the long-term effects of KGT could not be examined. Therefore, we will conduct a follow-up neuropsychological test 12 weeks after completing the treatment and observe any occurrence of AEs for 12 weeks after the treatment, compared to 4 weeks of post-intervention monitoring in the prior study.

The advantages of this trial include using extensive assessment tools to evaluate the outcomes. First, as in the pilot study, we will use SNSB, which is the full neuropsychological battery, which is composed of comprehensive and diverse cognitive tests, in order to sensitively capture the changes in cognitive function [13]. This is because the instruments frequently used in previous studies, such as MMSE and Alzheimer’s Disease Assessment Scale-Cognitive subscale, lack sensitivity in detecting mild degrees of cognitive decline, which lead to ceiling effects [18].

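### The primary outcome is described inconsistently (SNSB battery at weeks 24 and 36, battery including CDR, total SNSB-D to post-intervention), and the stated 5% error and 80% power belong only to the last

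*Protocol article*

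**What the plan says.** The protocol article describes the primary outcome in five places.

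- **Abstract, Methods:** "Primary outcomes will include changes in cognitive performance assessed using a neuropsychological test battery", compared "between the baseline, post-intervention visit, and follow-up visit (24th and 36th week, respectively"). The wording is plural, covers two post-baseline visits and names no score.
- **Outcome:** the primary outcome is change in cognitive performance, and "SNSB, which is composed of various cognitive tests such as CDR, GDS, and MMSE will be conducted to assess the cognitive function". Changes in the SNSB results are then analysed; no score or visit is named.
- **K-MMSE and SNSB:** "SNSB-II will be conducted at baseline, 24th week, and 36th week, to measure the effect of KGT on cognitive function", and "Changes in the mean SNSB scores will be analyzed as a primary outcome". The same section introduces the SNSB-D and its 300-point global cognitive function (GCF) total.
- **Sample size calculation:** "The primary outcome of interest in this study is the change in the total SNSB-D score between baseline and post-intervention". This is one score and one interval.
- **Discussion:** because the pilot showed improvement on CDR-SB, "the same neuropsychological test battery, including CDR, was selected as the primary outcome".

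Data analyses prescribes repeated-measures ANOVA, or the Friedman test, for the scores of the battery. It sets two-tailed p < 0.05 for all analyses. On populations it says "Efficacy analyses will be performed using the modified intention-to-treat (mITT) and per-protocol (PP) principles".

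**The concern.** A confirmatory trial needs one hypothesis to which its type I error and power are attached. Here the sections disagree on two things: whether week 36 is part of the primary outcome, and whether measures outside the SNSB-D total, such as CDR, belong to it. The analysis section does not settle either.

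At stake is how a positive result would be read. If total SNSB-D at week 24 missed significance but another battery score, or week 36, reached it, one section could be cited to call that a primary finding and another to deny it. The error rate and power in the sample size section would not describe such a claim.

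This does not depend on a separate analysis plan. The statements conflict within the article, and no analysis plan could follow all of them.

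**Working it through.** **Step 1. What does the sample size cover?** Inputs from Sample size calculation: d = 0.70, power 0.80, two-sided alpha 0.05, dropout 20%. Allocation and blinding gives 1:1.

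- Normal approximation: n per arm = 2(1.960 + 0.842)² / 0.70² = 32.04, rounded up to 33, so 66 in total. This matches the plan.
- Noncentral t: the solution is 33.02 per arm, and power at 33 per arm is 0.7997. This agrees for practical purposes.
- Dropout: 33 / 0.80 = 41.25, rounded up to 42 per arm, so 84. This matches the plan.

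The figure is therefore one two-group test of one score at one interval, with no allowance for a second test. The number itself is not in error.

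**Step 2. Is the powered score the same thing as the battery?** Table 3 lists everything in the SNSB-D total: attention 17 + language 27 + visuospatial 36 + memory 150 + frontal/executive 70 = 300. The points are fully used, and CDR, GDS and K-MMSE are not among the listed components. The Outcome section and the Discussion thus describe a primary measure that includes items the powered endpoint excludes.

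**Step 3. Do the visits agree?** The abstract gives weeks 24 and 36. Sample size calculation gives baseline to post-intervention, and the abstract identifies the post-intervention visit as week 24. They do not agree.

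**Step 4. How large could the effect on type I error be?** The article states no success rule, no number of primary tests and no correlations. The following assumes that any one result at unadjusted two-sided 0.05 would count. Quantity: P(at least one |z| > 1.96) under no effect, by simulation with 1,000,000 draws.

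| Assumed family | Assumed correlation | Chance of at least one false positive |
|---|---|---|
| Total SNSB-D at weeks 24 and 36 (2 tests) | 0.9 / 0.7 / 0.5 between visits | 7.0% / 8.3% / 9.1% |
| Total plus five domains, one visit (6 tests) | 0.9 / 0.7 / 0 between domains | 10% / 15% / 24% |

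In the second row the total is built as the sum of five domains with equal variance and equal correlation, because the GCF score is defined as that sum. Treating the six tests as independent, 1 − 0.95⁶ = 26.5%, is not possible for a total and its own parts.

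**Step 5. What would a plural primary cost?** With a Bonferroni split over two tests (alpha 0.025 each, d = 0.70 assumed for each, t-test), 41 per arm are needed. 41 / 0.80 = 51.25, rounded up to 52 per arm, so 104 recruited. With 33 per arm, power for each test would be 0.71.

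**The case against.** The best defence is that the article describes one outcome with increasing precision: first the battery, then the SNSB-D as the means of scoring it, then the total SNSB-D change, stated in the singular in the sample size section. This has force. One endpoint is named outright, and a single group-by-time test on total SNSB-D would be one test. It does not remove the week 36 discrepancy. It also does not explain why CDR is put forward in the Discussion when it lies outside the SNSB-D total, and Data analyses does not fix that single test.

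Several stronger readings are tempting and should not be made:

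- **CDR as a separate primary endpoint.** A reader might infer this from the Discussion. The text says only that the battery, of which CDR is a part, was selected.
- **Mean SNSB scores as a further rival endpoint.** The phrase can simply mean group means.
- **Success on any score, visit or population.** A reader might infer that the trial may be declared positive this way. No such rule is stated. The percentages above show what that rule would imply, not what the plan prescribes.
- **Two populations as added multiplicity.** Listing both mITT and PP is common, and ranking them is often left to the analysis plan. The same holds for a multiplicity procedure. Neither absence is the finding.
- **An inference about the pilot.** A reader might suspect that total SNSB-D was not significant there. The article does not give the pilot's arm sizes or that test result, so nothing should rest on it.

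**Conclusion.** The point holds as an internal inconsistency with consequences for a confirmatory claim. The abstract conflicts with the sample size section on visits. The Outcome section and Discussion conflict with it on which measures are primary. The analysis section leaves the conflict open. The 5% error and 80% power apply only to change in total SNSB-D from baseline to post-intervention.

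The size is conditional. If any primary result were allowed to count, the false-positive chance would be about 7–9% for the total at two visits, or about 10–24% for the total plus five domains at one visit. These figures rest on the assumed rule, the assumed test families and the assumed correlations. The conflict between the sections rests on none of them. The sample size is not wrong. The wording should be settled before unblinding.

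**What to change.** Use the same statement in the Abstract, Outcome, K-MMSE and SNSB, Sample size calculation, Data analyses and Discussion: the sole primary endpoint is the between-group difference in change of total SNSB-D (GCF) score from baseline to week 24.

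In Data analyses, tie it to one stated contrast and one named population, the mITT set already defined there. Make week 36, the domain scores, CDR, GDS and K-MMSE secondary, and label the PP analysis supportive.

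The cost is wording only, and recruitment stays at 84. The small downside is that a result on CDR, or at week 36, alone would no longer count as a primary success. If the sponsor prefers to keep week 36 as a second primary, the split in Step 5 gives the price: about 104 recruited instead of 84, under the assumptions stated there.

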**Discussion:**

This study aims to provide confirmatory evidence of the effect of the Korean herbal medicine, KGT, on improving cognitive function in patients with aMCI. We will identify the possible mechanisms underlying the effects of KGT using neuroimaging signals and blood biomarkers.

**Trial registration:**

Korean Clinical Trial Registry (https://cris.nih.go.kr/cris/search/detailSearch.do/16918; Registration number: KCT0007039; Date of registration: February 24, 2022).

**Supplementary Information:**

The online version contains supplementary material available at 10.1186/s12906-022-03805-9.

## Background

Mild cognitive impairment (MCI) is a transitional stage between the cognitive changes in normal aging and those found in dementia. It is characterized by self- or informant-reported cognitive complaints and objective cognitive decline with preserved independence in daily abilities [1]. Up to 60% of patients with MCI develop dementia within a 10-year period [2]. The amnestic form of MCI, in which memory loss is the predominant symptom, is associated with the pathology of Alzheimer’s disease (AD) and is often a prodromal stage of AD [3]. About 10–15% of patients with amnestic mild cognitive impairment (aMCI) progress to AD every year, and almost 50% of these patients convert to AD after 3 years [4]. Early intervention at the MCI stage may delay the progression to AD [5]. However, there are currently no effective pharmacological interventions for MCI [6].

Kami Guibi-tang (KGT) (*Kamikihito* in Japanese) and Guibi-tang (*Kihito* in Japanese) are traditional herbal formulae commonly used in Kampo and Korean medicine for the treatment of amnesia, loss of appetite, depression, and insomnia. A few experiments and clinical studies have examined how KGT may affect cognitive function, especially in mild AD. KGT improved learning performance in senescence-accelerated mice model [7] and ameliorated impairment of spatial memory induced by scopolamine [8]. It also improved deficits in object recognition memory in 5XFAD AD transgenic mice model [9]. A cross-over clinical trial showed that the Mini-Mental State Examination (MMSE) scores of patients with AD increased significantly during kihito intake period [10].

Since there was no previous data for patients with MCI, we conducted a pilot trial to explore the potential effect of KGT in aMCI patients and examined the feasibility of performing a large-scale trial [11]. Thirty-three aMCI patients took either KGT or placebo granules for 24 weeks, and the general cognition as measured by the Clinical Dementia Rating-Sum of Boxes (CDR-SB) was significantly improved in KGT group compared to the placebo group. The intervention was well tolerated with no severe adverse events. We designed a larger scale randomized clinical trial to validate the findings of our pilot study and further investigate the efficacy and safety of KGT for enhancing cognitive function, including memory performance of aMCI patients. We will also examine the effect of KGT on the progression to AD and investigate the possible underlying mechanisms using neuroimaging modalities, including resting-state functional magnetic resonance imaging (rs-fMRI) and task-based fMRI, and amyloid blood biomarkers.

## Methods

### Study design

This trial was designed based on our previous pilot study [11]. It will be a single-center, randomized, double-blind, placebo-controlled clinical trial with a 24-week intervention and a 36th week follow-up examination. It has been initiated at the Kyung Hee University Hospital at Gangdong, Seoul, Korea, in December 2021 and will be continued till May 2025. A flowchart of this trial is shown in Fig. 1. The schedules for enrollment, interventions, and assessments are presented in Table 1.

**Fig. 1 Fig1:**
[figure not shown]
Flowchart of the trial design

**Table 1 Tab1:**
[figure not shown]
Schedule of enrollment, interventions, and assessments

### Participants

#### Inclusion criteria

Participants who meet the following criteria will be included: (1) adults aged 55–90 years, with complaints of impaired memory; (2) objective cognitive decline as measured using the Seoul Neuropsychological Screening Battery (SNSB), with a score of 0.5 on the Clinical Dementia Rating (CDR), 3 on the Global Deterioration Scale (GDS), and a normal score on the Korean MMSE (K-MMSE); (3) diagnosed with amnestic MCI by a neurologist; (4) not taking any medication that could affect cognitive function (e.g., gliatilin, gliatamine, ginexin, tanamin, or other psychoactive drugs) within 2 weeks; (4) no change in medication for underlying diseases within 2 weeks, and no expected change in medication during the trial; (5) no difficulty in communication.

#### Exclusion criteria

Participants who meet any of the following criteria will be excluded: (1) diagnosed with AD according to the criteria of the National Institute of Neurological and Communicative Disorders and Stroke-Alzheimer’s Disease and Related Disorders Association (NINCDS-ADRDA); (2) diagnosed with vascular dementia according to the criteria of the National Institute of Neurological Disorders and Stroke-Association Internationale pour la Recherche et l’Enseignement en Neurosciences (NINDS-AIREN); (3) with brain disorders that cause neurologic symptoms, other than cognitive impairment; (4) with other neurodegenerative disorders (e.g., Huntington’s disease, Parkinson’s disease, Creutzfeldt-Jakob disease and Down’s syndrome); (5) cognitive decline due to other diseases (e.g., vitamin deficiency, brain tumor, head trauma, encephalitis, hypoxic brain damage, neurosyphilis); (6) with history of major depressive disorder; (7) with psychiatric disorders or behavioral problems requiring antipsychotic medication; (8) with history of convulsive disorder, except for febrile convulsions during childhood; (9) with life-threatening or unstable medical conditions; (10) uncontrolled hypertension; (11) with heart or renal diseases; (12) with edema; (13) gastrointestinal symptoms (e.g., diarrhea, nausea, anorexia, abdominal pain); (14) use of medication that may induce myopathy or hypokalemia; (15) with hypersensitivity to ingredients in study medication; (16) abnormal range of liver and kidney function (serum aspartate aminotransferase/alanine aminotransferase (AST/ALT) levels more than two-fold the upper reference limit, or serum creatinine (Cr) levels more than 10% of the upper reference limit); (17) participating in other clinical trials within 4 weeks; (18) with illiteracy; (19) those who are contraindicated for Brain MRI; (20) any other possible conditions considered inappropriate to participate in the trial.

